**SIRS**

Systemic Inflammatory Response (SIRS) Scale is used for evaluation of clinical improvement based on Heart rate, Mean arterial pressure(MAP mmHg), Respiratory rate / min, Blood oxygen saturation (SpO_2_ %）, body temperature（℃）, White blood cells (WBC *10^9^/L), Blood glucose (mmol/L) and Level of consciousness (Aware/awake, Lethargy or irritability, Shallow coma, coma, brain death). All these parameters except “Level of consciousness” are assigned a score from 0 to 4 based on the actual values recorded from patient corresponding to the range of values in Table no.1. For level of consciousness: Aware/awake (0), Lethargy or irritability (1), Shallow coma (2), coma (3), brain death (4).

**Table no.1: Systemic Inflammatory Response (SISR) Scale**

**NEWS2**

National Early Warning Score 2 (NEWS2) is commonly used for acute illness assessment based on aggregate scoring system from six physiological parameters which form the basis of scoring (respiration rate, oxygen saturation, systolic blood pressure, pulse rate, level of consciousness or new confusion, temperature). The magnitude of score allocated to every parameter shows its deviation from the normal. The score is summed and 2 points added for people requiring supplemental oxygen. The score is further categorized as: LOW score (an aggregate of 1–4), MEDIUM score (an aggregate of 5 or 6) and a HIGH score (an aggregate of 7 or more) [21].

**Clinical Observation**

**Before treatment (day -1 ~ 1):**

● Evaluation and recording of demographic data, vital signs (pulse, respiration, blood pressure, body temperature), blood oxygen saturation, and vital capacity.

● Medical history: including current medical history, past medical history and drug allergy history.

● Laboratory tests: coronavirus nucleic acid test, Complete blood count (CBC), Creatine kinase (CK), Lactate dehydrogenase (LDH), Pharyngeal swabs RT-PCR, Inflammatory cytokines, Inflammatory Markers (Erythrocyte sedimentation rate (ESR), C-reactive protein (CRP), Procalcitonin (PCT), Immune Markers (CD3, CD4, CD8).

● Radiologic examination: Chest CT

● Other tests: ECG

● Combined medications.

● Complete the 7-category ordinal scale and SIRS scale

**Treatment period (days 7, 14, 21)**

● Evaluate and record vital signs (pulse, respiration, blood pressure, body temperature), blood oxygen saturation and vital capacity

● Laboratory tests: coronavirus nucleic acid test, Complete blood count (CBC), Creatine kinase (CK), Lactate dehydrogenase (LDH), Pharyngeal swabs RT-PCR, Inflammatory cytokines, Inflammatory Markers (Erythrocyte sedimentation rate (ESR), C-reactive protein (CRP), Procalcitonin (PCT), Immune Markers (CD3, CD4, CD8).

● Radiologic examination: Chest CT

● Other tests: ECG

● Complete symptoms evaluation: SIRS scale score, the 7-category ordinal scale, and The National Early Warning Score 2 (NEWS2)

**Follow-up period (day 28)**

● Evaluate and record, vital signs (pulse, respiration, blood pressure, body temperature), blood oxygen saturation, vital capacity.

● Laboratory tests: coronavirus nucleic acid test, Complete blood count (CBC), Creatine kinase (CK), Lactate dehydrogenase(LDH), Pharyngeal swabs RT-PCR, Inflammatory cytokines, Inflammatory Markers (Erythrocyte sedimentation rate ( ESR), C-reactive protein ( CRP ), Procalcitonin ( PCT ), Immune Markers (CD3, CD4, CD8).

● Radiologic examination: CT scan of the lungs is available to those who have the condition

● Other tests: ECG

● Complete symptoms evaluation: SIRS scale score and 7-category ordinal scale.

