**Outcome measures**

The primary outcome measures will be time to positive-to-negative conversion of COVID-19 nucleic acid in pharyngeal swab, in days. The secondary outcome measures include nucleic acid test rate and recovery from symptoms , vital signs assessment, treatment adverse effects, Vital capacity, Oxygen saturation, Computed Tomography(CT), Complete blood count(CBC), Creatine kinase (CK) ,Lactate dehydrogenase (LDH), Pharyngeal swabs RT-PCR, Inflammatory cytokines, Inflammatory Markers (Erythrocyte sedimentation rate ( ESR), C-reactive protein ( CRP ),  Procalcitonin ( PCT )), Immune Markers (CD3, CD4, CD8) and SIRS scale scores measured at baseline, after 7 days, 14 days, 21 days, and 28 days of treatment.

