**Data collection tools**

Separate data collection forms are developed for trial data collection as: Medical history forms for taking relevant medical history, Case Report Form (CRF) to collect treatment related data, adverse events forms to collect data regarding any adverse event happening during the trial. For recording improvement in clinical symptoms 7-category ordinal, SIRS and NEWS2 scales will be used.

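### Day-28 CT is limited to an undefined subset although CT is listed as an outcome at that visit, and NEWS2 is not scheduled at baseline or day 28

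*Protocol*

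**What the plan says.** **CT.** The Outcome measures section includes CT in its list of secondary outcomes ("Vital capacity, Oxygen saturation, Computed Tomography(CT), Complete blood count(CBC" is part of that list) and closes the list with the time points "measured at baseline, after 7 days, 14 days, 21 days, and 28 days of treatment". The baseline visit schedules it without qualification: "Radiologic examination: Chest CT". The section on days 7, 14 and 21 carries the same unqualified entry. At day 28 the entry becomes "CT scan of the lungs is available to those who have the condition". Nothing in the protocol says what the condition is.

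**NEWS2.** Data collection tools says: "For recording improvement in clinical symptoms 7-category ordinal, SIRS and NEWS2 scales will be used". The visit lists then differ:
- Baseline: "Complete the 7-category ordinal scale and SIRS scale".
- Days 7, 14 and 21: all three scales.
- Day 28: "Complete symptoms evaluation: SIRS scale score and 7-category ordinal scale".

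NEWS2 is not in the secondary outcome list of the Abstract or of Outcome measures. It appears only as a data collection scale and in the day 7 to 21 visits. The Abstract gives baseline and 28 days as the points of blinded evaluation.

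**The concern.** The two CT statements cannot both be carried out. An outcome due at day 28 needs scans from both randomised arms, and the visit list offers them only to a subset. If membership of that subset depends on how the patient is doing, it depends on something that diathermy is meant to change. Comparing scanned patients then no longer compares randomised groups, and it can hide a benefit.

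For NEWS2, recording improvement normally means change from a starting value or status at the end of follow-up. The schedule provides neither, although the other two scales named in the same sentence are scored at all five visits.

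**Working it through.** **1. Schedule, set side by side**

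| Item | Baseline | Day 7 | Day 14 | Day 21 | Day 28 |
|---|---|---|---|---|---|
| CT, Outcome measures | yes | yes | yes | yes | yes |
| CT, visit lists | yes | yes | yes | yes | undefined subset |
| SIRS, visit lists | yes | yes | yes | yes | yes |
| 7-category scale, visit lists | yes | yes | yes | yes | yes |
| NEWS2, visit lists | no | yes | yes | yes | no |

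The CT rows disagree at day 28 only. NEWS2 is absent at the two visits that the Abstract names for blinded evaluation.

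**2. What selection could do to day-28 CT.** The protocol gives no CT score, so every input here is an assumption except the 205 patients per arm. Let severity be normal with SD 1 and higher values worse. The control mean is 0 and the experimental mean is −δ. A patient is scanned only if severity exceeds a threshold t. With λ(a) = φ(a)/(1 − Φ(a)):

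- control mean among scanned = λ(t)
- experimental mean among scanned = −δ + λ(t + δ)
- difference among scanned = λ(t) + δ − λ(t + δ)

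Take δ = 0.28, the standardised effect size in the Sample size section, borrowed here for scale only. At t = 0, λ(0) = 0.798 and λ(0.28) = 0.984, so the difference is 0.798 + 0.28 − 0.984 = 0.09 SD. The full set:

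| True δ | Controls scanned | Experimental scanned | Difference among scanned |
|---|---|---|---|
| 0.28 | 69% (142) | 59% (120) | 0.13 SD |
| 0.28 | 50% (about 102) | 39% (80) | 0.09 SD |
| 0.28 | 31% (63) | 22% (45) | 0.07 SD |
| 0.50 | 69% | 50% | 0.21 SD |
| 0.50 | 50% | 31% | 0.16 SD |
| 0.50 | 31% | 16% | 0.12 SD |

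With δ = 0 the formula gives 0, so there is no bias when there is no effect. A simulation under the same assumptions gave the same figures. If being scanned is unrelated to severity, the expected difference stays at δ and only the number of patients falls.

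**3. What the missing NEWS2 baseline costs.** Assume a 0.28 SD effect, a two-sided 5% test and 195 per arm (390/2). A comparison of post-treatment scores alone is unbiased under randomisation and has 79% power. Adjusting for a baseline with correlation ρ raises the standardised effect to 0.28/√(1 − ρ²):

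| ρ | Standardised effect after adjustment | Power |
|---|---|---|
| 0.3 | 0.294 | 82% |
| 0.5 | 0.323 | 89% |
| 0.7 | 0.392 | 97% |

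**4. Can NEWS2 be derived at baseline and day 28?** The protocol's NEWS2 section lists six parameters plus an addition for supplemental oxygen. Pulse, respiration, blood pressure, temperature and oxygen saturation are recorded at both visits. The SIRS form has a consciousness item but nothing for new confusion. The 7-category scale states supplemental oxygen explicitly only in categories 3 and 4. A derived score is therefore possible but approximate.

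**The case against.** A reader might infer that neither measure allows a valid comparison of improvement. The documents do not support that. CT is scheduled without condition at baseline and days 7, 14 and 21, so change in CT to day 21 can be compared between arms. NEWS2 can be compared at days 7, 14 and 21 without a baseline, in line with the post-intervention comparison of means in the Data Analysis Plan.

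A reader might also infer that two stated outcomes are affected. NEWS2 is not a listed outcome, and symptom improvement is still captured at every visit by the other two scales. This stands: only CT is an outcome contradicted by its own schedule.

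The selection argument depends on reading the condition as disease status or clinical indication. Feasibility is an equally possible reading, and then the loss is mainly precision. Nor does the calculation support a reversed effect or sicker scanned patients in the experimental arm. In the model the difference shrinks but still favours the experimental arm, and the scanned numbers themselves differ by arm.

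Finally, the Data Analysis Plan promises multiple imputation, and its model may be specified in an analysis plan not shown here. Imputation could help if being scanned is explained by observed data such as the day-21 CT. That is a fair reply to any claim that imputation must fail, but it does not remove the contradiction over who is scanned.

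**Conclusion.** Two defects stand. First, the day-28 CT entry contradicts the Outcome measures section and leaves the scanned group undefined. If scanning follows persisting disease or clinical indication, a comparison of scanned patients would attenuate a true 0.28 SD effect to roughly 0.07 to 0.13 SD. That range rests on a normal severity score, a sharp scanning threshold and 31% to 69% of controls scanned, none of which comes from the protocol. Second, NEWS2 is assigned to recording improvement but is not scheduled where change from baseline or day-28 status could be measured. The cost is precision and those two summaries, not the validity of the comparisons at days 7 to 21.

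The consequence is limited to one visit of one secondary outcome and one supporting scale. The primary outcome is untouched. Correction is still worthwhile because it is nearly free and prevents a day-28 CT result in a selected subset from being read as a randomised comparison.

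**What to change.** - **CT:** reconcile Outcome measures with the day-28 visit and define the condition. Make day 21, the last visit with CT scheduled for all, the final formal between-arm CT comparison. Report day-28 CT descriptively, with the number scanned in each arm and the reason for scanning where recorded.
- **NEWS2:** derive it at baseline and day 28 from the recorded vital signs, oxygen saturation, the SIRS consciousness item and the oxygen status implied by the 7-category scale. State that the derived score is approximate, because new confusion is not recorded and oxygen use is only indirect. Use derived baseline NEWS2 as a covariate in the NEWS2 comparisons, and fix this before unblinded data are seen.

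**Cost:** wording and one derived variable, with no new scans or tests. This matters because Trial status reports that recruitment has already ended. The downside is that the formal CT comparison ends one week earlier.

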**Criteria for termination of clinical trial**

During the intervention, if the participants have the following circumstances, the intervention must be suspended, specifically:

(1) For those with intolerable adverse events / serious adverse events, if the investigator judges that the risk to the patient on continuing to participate in the trial is greater than the benefit, the trial must be suspended and appropriate treatment measures should be taken in time.

(2) Patients who have exacerbated conditions after treatment, but should be included in the efficacy and safety analysis of the protocol set.

(3) Patients who changed mind about participation in the trial due to any reason or no more willing to participate.

The investigator or sponsor has the right to terminate the study in advance, but the patient must be consulted on the relevant matters of enrollment, report to the ethics committee, and explain the reason. The trial can be terminated early after obtaining consent. For subjects who are excluded or suspended early, the date and reason for the suspension shall be recorded in the corresponding table. Participants who are excluded or terminated early will not be replaced by new subjects, and once they withdraw from the trial, they will not be able to re-enter the study. All adverse events and abnormal laboratory indicators will be followed up to pre-treatment status or to no clinical significance.

Once the trial is terminated, all research materials (including completed, partially completed, and blank case report forms), research equipment, and research drugs shall be returned to the sponsor.

**Preservation of case report form**

The primary researcher will keep all the detailed original documents of the subjects, and record in the case report forms the treatment progress, medication, laboratory inspection data, safety data, and efficacy evaluation timely and clearly. Case report forms, original documents, medical records, etc. should be clear, detailed, and easily identifiable by personnel participating in this clinical trial. The lead investigator will sign the confirmation and completion pages of the case report forms to verify the accuracy and completeness of all data. The case report forms and the original files will only be modified by the investigator. Any modification to the case report forms and the original file must not obliterate the original data. The correct modification method is to draw a single line on the original data, then write the modified data next to the original data, and sign the date and the initials of the person who modified it.

The trail data shall be retained for 10 years after the end of the trial. However, if required by current regulations or an agreement with the sponsor, this information should be kept for a longer period of time.

**Adverse event records, reports and treatments**

**1. Definition of adverse events**

An adverse event is any undesired medical event that occurs during or after treatment to a patient in a clinical study. All adverse events do not necessarily have a causal relationship with the treatment. Since short wave diathermy is routinely practiced for pneumonia treatment in our rehabilitation department, no large scale adverse events have been found in routine treatments of pneumonia.

**2. Reporting requirements**

Researchers will evaluate each adverse event to determine whether it meets the criteria for serious adverse events. If a serious adverse event occurs, it will be reported quickly in accordance with national regulations. All adverse events will be recorded on the adverse event page of the case report form. It should be noted that the report form used to collect information on serious adverse events is different from the case report form that just has a page “adverse event record page” for recording adverse events. The serious adverse events report form is shown in the appendix. In addition, because the data collected are same, the two forms must be filled accordingly. For example, the same adverse event terms should be used in both forms. Regardless of whether filling out a medical report form or an adverse event report form, same adverse event terms and accurate medical terms should be used in reporting adverse events.

**3. Reporting requirements for serious adverse events**

If a serious adverse event occurs during the trial, regardless of its relation to the treatment method, relevant treatment measures will be taken immediately and reported to the main investigator ([name]), project leader and ethics committee (Ethics Committee of Tongji Hospital of Huazhong University of Science and Technology) within 24 hours.

**Statistical methods**

Data collection will be performed after the patient is discharged from the Hospital, and completed by the study data collector separately; a member of the study team, blinded to the intervention groups. Adjudication of any conflicting data points will be identified by the study statistician and reviewed in tandem by the data collector to settle any discrepancies. The data will be available upon reasonable request from the corresponding author.

**Data Analysis Plan**

The principles of intent-to-treat analysis will be followed to include all participants randomised for the study. Data normality will be assessed using the Kolmogorov-Smirnov (K-S) and Shapiro-Wilk (S-W) tests. The missing data will be managed by multiple imputations. Descriptive statistics: mean, median, maximum, minimum, confidence interval, and standard deviation will be calculated for continuous data, and frequency distributions will be calculated for categorical data. Prevalence of negative and positive tests will be calculated at specific time points. Independent t test will be used to compare the means after intervention between the two groups in case of normal distribution of data. If the data was not normally distributed Mann Whitney test will be used. Chi-square test will be used for comparison of categorical data between the two study groups.

Linear regression analysis will be used to evaluate any relationship between age, gender and study groups and the primary (time to positive-to-negative conversion of COVID-19 nucleic acid test) and some secondary variables. Adjusted and unadjusted analysis will be performed. Compliance analysis: Statistics whether the patients were treated with short wave on time. According to the requirements of the adverse reaction correlation, we will list the adverse events and adverse reactions of the two groups (including the number of various adverse events, laboratory testing indicators before and after the treatment "normal to abnormal" or” "Aggravated abnormally"), the number of cases and the rate of change, list the reasons and explain. Chi-square test will be used for statistical analysis of adverse reactions. Within the group and between the groups analysis will be performed using 95% confidence internal and a p value of 0.05. Analysis of influencing factors: If there are significant differences between the two groups before treatment, such as age, gender, disease type, and condition, or there are related factors (such as combined medication) that significantly affect the effects of treatment during the treatment, the comparison of the efficacy, these factors will be considered as covariates, and analysis of covariance or logistic regression will be is used. The analyzed data will mainly be expressed in the form of self-explanatory tables with statements, table notes. The results of repeated measurement data will be expressed in both tables and statistical charts to increase readability.

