**Abstract**

**Background**

Arising pathogens are a worldwide challenge for [healthful living](https://www.thesaurus.com/browse/healthful%20living). Severe acute respiratory syndrome coronavirus 2 (COVID-19) is an enveloped RNA virus that distributed dramatically among humans. COVID-19 mainly attacks the respiratory system leading to severe acute respiratory syndrome and pneumonia. Some Rehabilitation modalities such as short waves diathermy could be of help in supporting the medical treatment and avoiding complications of COVID-19 pneumonia.

**Methods/design:** This is a single center, evaluator blinded, parallel design randomised, controlled clinical trial study protocol based on SPIRIT guidelines. A Randomization plan will be created online on [www.randomization.com](http://www.randomization.com) by a statistician who will not be part of the study. Small blocks of various sizes will be used. A total of 410 patients will be randomised in 1:1 ratio to two groups: experimental group (n=205) and control group (n=205) by permuted blocks method. The primary outcome measures will be time to positive-to-negative conversion of COVID-19 nucleic acid test in pharyngeal swab, in days assessed at 7^th^, 14^th^ ,21^st^ and 28^th^ day. The secondary outcome measures include nucleic acid test rate and recovery from symptoms, Vital signs assessment, Computed Tomography, Complete blood count, Creatine kinase, Lactate dehydrogenase, Inflammatory cytokines, Inflammatory Markers, Immune Markers and SIRS scale scores. Blinded evaluation will be at baseline (the day of starting ultra-short-wave diathermy) and after 28 days following the interventions.

**Objective:** To evaluate the therapeutic effects of ultra-short-wave diathermy (SWD) on COVID-19 pneumonia.

**Discussion**: This clinical trial will be the first randomised controlled clinical trial to comprehensively examine the efficacy of ultra-short-wave diathermy on COVID-19 pneumonia patients. The results may provide quality evidence of the role of ultra-short-wave diathermy in improving outcomes and avoiding complications of this viral infection.

**Clinical Study registration:** This randomised controlled trial had been prospectively registered with the Chinese Clinical Trials (ChiCTR2000029972) at 17, February ,2020. URL: http://www.chictr.org.cn/historyversionpuben.aspx?regno=ChiCTR2000029972

**Keywords**: COVID-19, coronavirus, Ultra short-wave diathermy, Pneumonia

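### The primary outcome, days to a negative swab, is read weekly and cut off at day 28, but the plan analyses it as a fully observed continuous value and gives no rule for patients who never convert

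*Protocol*

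**What the plan says.** **Outcome.** Outcome measures: "The primary outcome measures will be time to positive-to-negative conversion of COVID-19 nucleic acid in pharyngeal swab, in days". The Methods/design part of the Abstract adds the reading times: "in days assessed at 7^th^, 14^th^ ,21^st^ and 28^th^ day". The visit lists agree. Nucleic acid tests fall on days 7, 14 and 21 in the treatment period and on day 28 at follow-up, which is the last visit.

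**Analysis of this outcome.** Data Analysis Plan: "Linear regression analysis will be used to evaluate any relationship between age, gender and study groups and the primary" outcome, with conversion time named in brackets straight after. This is the one sentence that explicitly links a method to the primary outcome.

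**Analysis of continuous data in general.** The same section applies Kolmogorov-Smirnov and Shapiro-Wilk tests first. Then: "Independent t test will be used to compare the means after intervention between the two groups in case of normal distribution of data". If normality fails, Mann-Whitney is used.

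**Population and missing data.** All randomised participants are analysed by intention to treat. "The missing data will be managed by multiple imputations".

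No survival method, censoring rule or rule for death before conversion is named. The prevalence of positive and negative tests at set time points is planned, and chi-square is named for categorical data.

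**The concern.** The data never contain an exact conversion day. Each patient yields one of five results: converted by day 7, by 14, by 21, by 28, or not converted by day 28. The last group is right-censored, and a patient who dies while still positive never has a conversion time.

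Linear regression and a t test need a number for every patient. Mann-Whitney needs at least a rank. For non-converters the protocol supplies neither. Imputation is the only tool it names, and it does not fit: a positive swab on day 28 is an observed result, and imputing a conversion time replaces it with an event that was not seen.

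The headline estimate is at stake. Two analysts following the same text could drop these patients, enter 28, rank them last or impute them, and report different effects.

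**Working it through.** **1. How the trial was sized.** Inputs from Sample size: effect 0.28, α = 0.05 (sidedness not stated), 80% power, N = 390. For two means, two-sided, n per arm = 2(1.96 + 0.842)² / d².
- d = 0.28: 2 × 7.85 / 0.0784 = 200.2, so 201 per arm, 402 in total (404 with the t distribution).
- N = 390 corresponds to d = 0.2844, which rounds to 0.28. At exactly 0.28, 195 per arm gives 78.8% power.

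So 390 reproduces, allowing for rounding, as a comparison of two means of fully observed values. Sizing and analysis share the same premise.

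**2. What each unstated coding does.** The documents give no conversion rate, so these are assumptions: exponential conversion times, readings at days 7, 14, 21 and 28, 195 per arm, hazard ratio 1.35, no deaths, 2,000 simulated trials. With a control median of 12 days, the share not converted by day 28 is 2^(−28/12) = 20% in controls and 2^(−28 × 1.35/12) = 11% in treated patients.

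| Control median (days) | Grouped log-rank | t test, non-converters = 28 | Mann-Whitney, worst rank | t test, converters only |
|---|---|---|---|---|
| 8 | 81% | 77% | 74% | 47% |
| 12 | 76% | 70% | 70% | 26% |
| 16 | 74% | 66% | 70% | 16% |
| 20 | 70% | 58% | 66% | 12% |

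At a median of 12 days the mean difference is 2.1 days with 28 entered and 1.1 days among converters only. With equal conversion and no deaths, every method rejected in 4.4% to 6.0% of trials, so false positives are not the problem in that setting.

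**3. The protocol's own effect size.** Assumptions: gamma times (shape 1, 2 or 4), control mean 12-20 days, treated mean lower by 0.28 control SDs, same weekly grid, 195 per arm.
- Grouped log-rank: about 78-86% power.
- All patients, with 28 or a worst rank for non-converters: about 72-83%, a loss of roughly 0-10 points.
- Converters only: about 25-73%. The mean difference falls from about 1.6-2.3 days (28 entered) to 1.1-1.5.

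**4. An effect on never converting.** Assume 10% v 20% not converted by day 28 and equal speed among converters.
- Converters only: rejects about 5% of the time, no better than chance.
- All-patient t or Mann-Whitney: about 37-54%.
- Grouped log-rank: about 67-71%.
- Chi-square on day-28 status: pooled proportion 0.15, null SE = √(2 × 0.15 × 0.85/195) = 0.0362, alternative SE = √((0.09 + 0.16)/195) = 0.0358. Then z = (0.10 − 1.96 × 0.0362)/0.0358 = 0.81, or about 79% power.

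**5. The normality gate.** With non-converters entered at 28 the outcome has four possible values; with a separate code it has five. Shapiro-Wilk rejected normality in every simulated sample. For this outcome the t test branch would in practice not be used, and the gate decides nothing.

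**6. Deaths.** With the same conversion hazard in both arms, a control median of 12 days and assumed 28-day death risks of 3% (control) v 10% (treated), the log-rank test that keeps deaths as not converted rejected 9% of the time. The death rule is thus part of the question being asked and has to be written down.

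**The case against.** Several stronger readings are tempting. The protocol does not support them.

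- *The trial would lose most of its power.* A reader might infer this from the converters-only figures. Those come from dropping patients, which the plan's own intention-to-treat statement rules out. If everyone is kept, the loss is modest: roughly 0-10 points in the gamma scenarios, and 12 at worst in the table.
- *Entering 28 is simply wrong.* It is not. With follow-up complete to day 28, the mean of min(T, 28) is a restricted mean time, and a worst-rank Mann-Whitney is a valid test. Both are less efficient here. The defect is that neither is stated.
- *An effect on never converting would be invisible.* The test rate is a secondary outcome and chi-square is named for categorical data. Day-28 status has about 79% power in step 4. The effect would show, but outside the primary analysis.
- *Imputation has been shown to bias the result.* No imputation was simulated, and the protocol does not say that a patient positive at day 28 counts as missing. The objection to imputing is one of principle.
- *Deaths will drive the result.* Eligibility is limited to ages 18-65 and excludes respiratory failure, ventilation, shock and multiple organ failure needing ICU care. Deaths may be few, and no rate is given.

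It is also fair to say that the t test sentence does not name the primary outcome. The link there is its continuous-data wording; the regression sentence supplies the explicit one.

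A statistical analysis plan could add a censoring rule. It could not make linear regression suit this outcome without departing from the protocol. The mismatch between outcome and method stands.

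**Conclusion.** Wrong as written. The protocol assigns an uncensored continuous-data method to a time to event that is grouped by week and censored at day 28. It leaves the value for non-converters and deaths to an unstated choice.

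The consequence is an analyst-dependent primary estimate and some loss of power. The loss is small if all patients are kept under a sensible code. It is large, with an attenuated difference, only if non-converters are dropped. Type I error is not inflated when conversion is equal and no one dies.

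Every percentage rests on assumed conversion distributions, because the documents give no conversion, death or never-converter rate. That the outcome and the method do not match needs no such assumption.

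**What to change.** In the Data Analysis Plan:

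1. Name one time-to-event analysis that respects the weekly grid as primary. One example is a grouped log-rank test with a discrete-time complementary log-log model or an interval-censored proportional-hazards model, reporting the hazard ratio with its 95% confidence interval.
2. Censor patients still positive at day 28 at day 28.
3. State how death before conversion enters the analysis, for example kept as not converted through day 28, or as a competing event.
4. Limit multiple imputation to swabs truly missed in living patients.
5. For the primary outcome, remove the normality gate, the t test or Mann-Whitney, and linear regression.

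**Cost.** Wording only: no new data and no new patients. It should be settled before unblinding. Trial status says recruitment is complete, so N is fixed. The 0.28 in Sample size is a two-mean quantity, so the stated power should be re-expressed for the new analysis. As a guide, events needed = 4(1.96 + 0.842)² / (ln HR)², which is 349 at a hazard ratio of 1.35. If 60% to 100% of 390 patients convert (234 to 390 events), power is 63% to 84% at 1.35, 52% to 74% at 1.30 and 73% to 91% at 1.40. These hazard ratios are assumptions, since the protocol gives none.
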